Despite recommendation by national agencies such as the National Institute for Health and Care Excellence, the European Society of Cardiology and the American College of Cardiology (ACC)/American Heart Association (AHA),^2–5^ scoring systems which objectively characterise cardiovascular risk are not systematically applied to the management of NSTEACS.^12^ The Global Registry of Acute Coronary Events (GRACE) risk score tool is specifically designed for the risk stratification of patients with acute coronary syndrome (ACS), is aligned to treatment recommendations and, compared with other ACS risk scores, has superior discriminative performance.^13 14^ It was developed in an international registry programme to predict in-hospital and 6 month death or non-fatal myocardial infarction (MI) in a broad spectrum of ACS patients, and has since been derived and validated for these outcomes in over 42 000 patients with external validation in other cohorts.^15 16^ For clinical use, a simplified model was derived that predicts the risk of death alone, and the composite outcome of death or non-fatal MI, based on eight variables (age, heart rate, systolic blood pressure, Killip class, creatinine concentration, elevated biomarkers of myocardial injury, cardiac arrest on admission and ST-segment deviation). These factors conveyed more than 90% of the total risk and had a c-statistic of 0.81 for predicting death and 0.73 for predicting death or non-fatal MI from admission to 6 months after discharge.^17^ The GRACE risk score also shows good discriminatory performance for mortality at up to 2 years following discharge from hospital with ACS.^18^ The GRACE risk score has been updated (http://www.outcomes-umassmed.org/grace/) and shows good predictive accuracy of 1 year and 3 year mortality across a spectrum of ACS types.^19 20^

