#### Randomisation and blinding

Eligible hospitals (clusters) will be centrally randomised by the Leeds Clinical Trials Research Unit (CTRU) 1:1 to either GRACE risk score guided management or standard care using minimisation with a random element, aiming to ensure the cluster composition of each study arm is similar with respect to cluster-specific volume of patients hospitalised with ACS and primary percutaneous coronary intervention (PCI) capability. Site staff will not be blind to their assigned intervention, nor will recruited participants be blind to the intervention assigned to that site. Once a hospital has been randomised to the use of the GRACE risk score tool or to standard care, informed of their allocation and completed site initiation as required for their arm, a run-in phase will take place. During this time (up to 3 months for each site), the data collection and quality will be evaluated and the frequency of GRACE application in the intervention arm sites will be measured, as patients are recruited. (figure 1).

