**creatine kinase**-muscle/brain (CK-MB) 2x URL; or,If there is no CK-MB available, then total CK greater than the local URL(c) Documented coronary artery disease:History of myocardial infarction (MI) or angina;Congestive cardiac failure due to ischaemia;Resuscitated sudden cardiac death;Prior or new positive stress test with or without imaging;Prior or new, cardiac catheterisation, percutaneous coronary artery intervention or coronary artery bypass graft surgery documenting coronary artery disease(d) **At least** two of the following High Risk features:Haemodynamic compromise (systolic blood pressure <90 mmHg and heart rate >100 bpm)Left ventricular systolic dysfunction (left ventricular ejection fraction <0.40);Presence of known diabetes mellitusDocumentation of chronic kidney disease (estimated glomerular filtration rate <60mls/min/m^2^)3. Willing and able to provide written informed consentParticipant exclusion criteriaPatients presenting at hospital due to an acute ST-segment elevation myocardial infarctionPatients presenting at hospital with an acute coronary syndrome accompanied with, or precipitate by significant comorbidity for example, motor vehicle accident, trauma, severe gastrointestinal bleedingPerioperative or periprocedural MIPatients already recruited into the studyPatients not living in the UK

The site Principal Investigator or a delegated member of the clinical research team will undertake the informed consent process. The participant will be approached within 12 hours of hospital admission (ideally in the emergency department or acute admission ward, whichever is closer to the time of hospitalisation), allowed time to consider the information and ask questions before deciding whether to participate. An optional oral consent pathway is available where participants will be provided with a shortened document describing the UKGRIS trial and after discussing the trial with the research nurse, can verbally consent to commence the care assigned to the admitting hospital. In hospitals allocated to GRACE, risk scores will be calculated and treatment recommendations made. Thereafter, the patient will be approached for full written informed consent. Participants who give oral consent at this point will be registered and complete the self-reported questionnaire and frailty score. Participants who give oral consent and refuse written informed consent will be excluded, and completed case record forms (CRFs) destroyed.

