†Baseline assessments are: age, sex, ethnicity, height, weight, date and time of symptoms onset and admission to hospital, ECG ST-segment deviation, heart rate on admission, systolic blood pressure on admission, Killip class, diuretic usage, creatinine, troponin (date, time and elevated), cardiac arrest occurrence, haematocrit, peripheral vascular disease, diabetes mellitus, congestive cardiac failure.

CRUSADE, Can Rapid risk stratification of Unstable angina patients Suppress ADverse outcomes with Early implementation of the ACC/AHA Guidelines; GRACE, Global Registry of Acute Coronary Events.

**Table 2 T2:** Definitions of UKGRIS outcome measures and primary analyses

Outcome measure	Assessed at	Analysis method

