**Co-primary**		
(1) Number of class I guideline indicated processes received per patient (see online supplementary file 2 for full description)	Discharge	Logistic regression, modelling agreement between eligibility and receipt of process as function of treatment arm, including fixed effects for minimisation factors, random hospital effect and random patient effect.
(2) Time from registration until first occurrence of one of the following * cardiac death, * new onset heart failure, * non-fatal MI, or * cardiovascular hospitalisation	12 months post registration	Kaplan-Meier survival estimates; appropriate time-to-event regression (eg, proportional hazards, flexible parametric model^47^) including fixed effects for minimisation factors and random hospital effect, (sensitivity analysis: also accounts for competing risks of non-cardiac death and withdrawal from follow-up.)

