#### Analysis methods

A full statistical analysis plan will be finalised prior to any comparative analyses, following the guidelines of Gamble *et al*.^36^ The statistical analysis plan will describe the derivation of outcomes, define analysis populations and detail the analyses of each outcome measure. In brief, analyses will take the form of generalised linear models that include fixed effects for the minimisation/stratification factors and random effects for the recruiting hospitals (the random effects distribution with the best statistical fit will be used for analysis) to reflect the cluster-randomised nature of the trial (table 2). The derivation of the primary outcome measure is defined in online supplementary file 2. Additional exploratory subgroup analyses are planned for the primary endpoint: analysing guideline uptake according to intervention type (invasive, non-invasive, behavioural and pharmacotherapies); subgroup effects will investigate interaction between treatment arm and age, gender, diabetes, heart failure, initial hospital type, frailty, comorbidity and estimated bleeding risks, among others. Analyses will use the full analysis set comprising all registered participants analysed according to their randomised hospital as intention to treat (patients will only be excluded if informed consent was not given, or if participants request that their data not be used in any analysis). Further supporting randomisation-respecting efficacy analyses may be considered, in particular, a mediation analysis^37^ to estimate the net direct and net indirect effects of a non-NSTEACS final diagnosis on receiving class I guideline therapies. The statistical analysis plan will include an agreed strategy for imputing missing data items (using multiple imputation, where appropriate^38 39^), including handling incomplete EHR on cardiovascular registries and other data sources to determine whether absent records indicate no events.

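### Unblinded staff recruit patients after hospitals know their allocation, yet the stated co-primary models adjust only for two hospital-level factors and no patient-level baseline risk

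*Protocol article*

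**What the plan says.** The section on randomisation and blinding sets the order of events: "Once a hospital has been randomised to the use of the GRACE risk score tool or to standard care, informed of their allocation", with patient recruitment following. It adds: "Site staff will not be blind to their assigned intervention, nor will recruited participants be blind to the intervention assigned to that site". Under Eligibility criteria, consent is individual and taken locally: "The site Principal Investigator or a delegated member of the clinical research team will undertake the informed consent process". The same section allows assigned care to start on oral consent. Patients who later decline written consent are removed and their forms destroyed.

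Table 2 lists the primary analyses. For co-primary (2) the regression is specified as "including fixed effects for minimisation factors and random hospital effect". For co-primary (1) it is the same set plus a random patient effect. Analysis methods repeats the general form: "fixed effects for the minimisation/stratification factors and random effects for the recruiting hospitals". The minimisation factors are hospital ACS volume and primary PCI capability.

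The baseline list in the Table 1 footnote covers all eight GRACE components, including "ECG ST-segment deviation, heart rate on admission, systolic blood pressure on admission, Killip class", together with sex and diabetes. Frailty is also assessed at registration. Of the simplified GRACE model, Background says its factors "had a c-statistic of 0.81 for predicting death and 0.73 for predicting death or non-fatal MI". Analysis methods uses patient-level factors in exploratory subgroup interactions. The only patient-level covariate in Table 2 is baseline EQ-5D-5L, in a secondary model.

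**The concern.** In a cluster trial, randomisation balances hospitals. It balances patients only if the arm cannot influence who is recruited. Here it can: the people who approach and consent patients know the allocation, and so do the patients. A further loss, of patients who give oral but not written consent, can occur after allocated care has begun. If intervention and control hospitals consent patients of different risk, the arm contrast mixes case-mix with the effect of the tool. A covariate set made only of hospital attributes cannot correct this. A random hospital or patient effect does not correct it either, because such terms model correlation rather than a systematic difference between arms.

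Both co-primary endpoints are exposed in principle. For the clinical composite, baseline risk drives events. For guideline uptake, Background describes a paradox in which lower-risk patients are more likely to receive invasive care, and the Discussion names frailty as a possible reason for non-receipt. Leaving out strong predictors also gives up precision that the trial has already paid to collect.

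**Working it through.** **1. The plan's own figures.** Sample size states 14 clusters of 100 per arm for each co-primary endpoint. With (1.960 + 0.842)² = 7.849 and the standard unmatched cluster formulas based on the coefficient of variation k:

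- Co-primary (1): c = 1 + 7.849 × [(0.95×0.05 + 0.98×0.02)/100 + 0.02² × (0.95² + 0.98²)] / 0.03² = 1 + 7.849 × 0.001416 / 0.0009 = 13.35, rounded up to 14.
- Co-primary (2), with 27 months giving y = 225 person-years per cluster: c = 1 + 7.849 × [(0.13 + 0.104)/225 + 0.05² × (0.13² + 0.104²)] / 0.026² = 1 + 7.849 × 0.001109 / 0.000676 = 13.88, rounded up to 14.

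Both reproduce and are not in dispute here. Neither allows for arms that differ in patient risk.

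**2. Covariates against the source of imbalance.**

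| Item | Level | In co-primary models? |
|---|---|---|
| ACS volume, primary PCI capability | hospital | yes, fixed effects |
| Hospital | hospital | yes, random effect |
| Patient, co-primary (1) only | patient | yes, random effect |
| Age, sex, diabetes, GRACE components, frailty | patient | no |

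Selection would act at patient level. No fixed effect in the stated models acts there.

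**3. Illustration using a risk score.** Inputs from the article: 13% control rate and a target difference of 13 − 10.4 = 2.6 points. Assumed inputs: a mean imbalance of 0.1 SD, and the score's c-statistic for this composite. The article's 0.73 is for death or non-fatal MI to 6 months after discharge. The composite runs to 12 months and also counts heart failure hospitalisation and cardiovascular readmission, so 0.60 and 0.65 are shown as well.

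Under an equal-variance normal model the log-odds per SD are b = √2 × Φ⁻¹(c). The intercept a is set so that the average of expit(a + bZ) over Z ~ N(0,1) equals 13%. Z is then shifted down by 0.1.

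| c (assumed for the composite) | b | Rate after 0.1 SD shift | Shift in points | Share of 2.6 |
|---|---|---|---|---|
| 0.60 | 0.358 | 12.61% | 0.39 | 15% |
| 0.65 | 0.545 | 12.42% | 0.58 | 22% |
| 0.73 | 0.867 | 12.13% | 0.87 | 34% |

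A shortcut moves one logit without averaging. At c = 0.73, logit(0.13) − 0.0867 gives 12.05%, a shift of 0.95 points or 37%. That slightly overstates the shift, so the averaged figures are used.

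**4. Second illustration, one binary factor.** Assume no true effect, a factor with 40% prevalence in control, a factor rate ratio R, and prevalence lower by d in the GRACE arm. The spurious rate ratio is [1 + (0.4 − d)(R − 1)] / [1 + 0.4(R − 1)].

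- R = 1.5, d = 0.05: 1.175/1.20 = 0.979, or 9% of the target on the log scale (log 0.979 / log 0.80).
- R = 2, d = 0.10: 1.30/1.40 = 0.929, or 33%.
- R = 3, d = 0.10: 1.60/1.80 = 0.889, or 53%.

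With 15 clusters of 100 per arm, k = 0.05 and one year per patient, a nominal 5% test would reject in about 5.5%, 11% and 20% of trials respectively.

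**The case against.** The strongest counter-argument is about reach. Analysis methods introduces the models in brief and defers detail to an analysis plan that is not shown. The models are said to include these terms, not to be limited to them. That lowers confidence that the set is exhaustive. It does not remove the point: Table 2 is headed as giving the primary analyses, the covariate set appears twice, and a baseline covariate is named where one was wanted (EQ-5D-5L). It reads as a stated choice.

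Several further points stand and limit the finding:

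- **Co-primary (1).** The outcome is agreement between eligibility for and receipt of each process, so part of case-mix is already in the outcome. No bias has been quantified for this endpoint.
- **Safeguards.** Non-registration logs, efforts at broad recruitment in both arms and registry data on non-participants are described. They bear on how likely the bias is, but the article ties no analysis to the logs.
- **Differential recording.** The baseline fields are recorded by unblinded staff. Killip class, ST deviation and frailty could be graded or completed differently by arm, so adjusting for them carries its own risk.
- **Estimand.** Adding strong covariates to logistic or hazard models makes the effect conditional.

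A reader might infer that biased recruitment has been shown, that adjustment would correct it, or that the prognostic data go unused altogether. The article supports none of these. It gives no baseline comparison by arm, adjustment handles only measured factors, and some of these factors do enter exploratory subgroup analyses.

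**Conclusion.** The point holds as a moderate recommendation. The design leaves patient-level balance unprotected, and the co-primary models as stated contain nothing at patient level that could reduce an imbalance, although suitable variables are collected in both arms.

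The size cannot be fixed from the article, which gives neither the magnitude nor the direction of any imbalance. A 0.1 SD difference would be worth roughly 0.4 to 0.9 points on a 13% rate, assuming that the score's c-statistic for the composite lies between 0.60 and 0.73. A reader might take 0.73 as applying directly to the composite; the article reports it for a narrower outcome, so the upper end is not established. The figures concern co-primary (2) only. A gain in precision is expected but has not been quantified.

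**What to change.** In Table 2 and the analysis plan, before any comparative analysis:

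- **Add covariates.** Pre-specify a small set of patient-level baseline covariates in the co-primary (2) model, and likewise in co-primary (1): age, sex, diabetes and the GRACE components. A GRACE score could replace the components if it is derived centrally from the baseline fields in both arms. Data collection says that site-calculated scores are recorded only in intervention hospitals.
- **Keep the existing terms.** Retain the minimisation factors and the random effects, and report the minimisation-only model alongside.
- **Guard against differential recording.** Favour objectively recorded fields (age, sex, creatinine, heart rate, systolic blood pressure, diabetes). Check in a sensitivity analysis the fields open to differential grading (Killip class, ST deviation, frailty).
- **Look for the bias.** Compare baseline risk and the non-registration logs by arm.
- **State the limits.** Say that adjustment reduces but cannot remove recruitment bias, and that the hazard and odds ratios become conditional on the covariates.

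The cost is a little analysis work, imputation of missing baseline items (multiple imputation is already foreseen) and a conditional estimand. No new data are needed.

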**Secondary**		
(1) Health-related quality of life (EQ-5D-5L utility)	12 months post registration	Linear regression, (with data transformed, if necessary) including fixed effects for minimisation factors and baseline value with random hospital effect.
(2) Number of days in hospital within 12 months	12 months post registration	Linear regression (with data transformed, if necessary) including fixed effects for minimisation factors and random hospital effect.
(3) Time until first occurrence of each component of the composite co-primary endpoint (co-primary (2)). Performed separately for each of the four components.	12 months post registration	Kaplan-Meier survival estimates; time-to-event regression including fixed effects for minimisation factors and random hospital effect, accounting for (sensitivity analysis: competing risks of non-cardiac death and withdrawal from follow-up.)
(4) Unscheduled revascularisations. Any admission (1=Yes, 0=No) for an unplanned PCI or CABG within 12 months of registration.	12 months post registration	Logistic regression, including fixed effects for minimisation factors with random hospital effect.

CABG, coronary artery bypass graft; MI, myocardial infarction; PCI, percutaneous coronary intervention; UKGRIS, UK GRACE Risk Score Intervention Study.

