### Statistical methods

#### Sample size

A minimum of 30 clusters, each recruiting 100 participants (ie, 3000 in total) will give 80% power to detect clinically relevant differences in the co-primary endpoints with two-sided 5% significance tests (see sections 7.2.1 and 7.2.3 of^34^). For the proportion of class I guideline-recommended therapies implemented, this assumes 95%^35^ of recommended therapies implemented in the control arm and will detect an absolute increase of 3% to 98% in the GRACE arm, with an assumed coefficient of variation (CV) in cluster outcomes of 0.02. For time to first cardiac outcome, a fixed recruitment of 15 clusters of 100 patients per arm gives 80% power to detect a difference in 12 month rates of 13% and 10.4% between standard care and GRACE arms, assuming a mean follow-up of 27 months and CV of cluster event rates of 0.05. Both endpoints require 14 clusters of 100 patients in each arm to have 80% power, though no adjustment for multiple testing was made. Recruiting 15 clusters per arm allows for attrition of 7% to 10%. For more details, see online supplementary file 3. Additional sites have been and will be opened to ensure that target recruitment is achieved, and to safeguard study power should these assumptions not be met.

10.1136/bmjopen-2019-032165.supp3Supplementary data

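### Table 2's competing-risk sensitivity analyses list withdrawal, which is censoring, and omit cardiac death for the three non-fatal components

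*Protocol article*

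**What the plan says.** Table 2 of the protocol article sets the analysis of two sets of time-to-event outcomes.

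- **Co-primary (2)** is time from registration to the first of "cardiac death, * new onset heart failure, * non-fatal MI, or * cardiovascular hospitalisation". The main analysis is Kaplan-Meier estimation with a time-to-event regression. A bracket then adds: "sensitivity analysis: also accounts for competing risks of non-cardiac death and withdrawal from follow-up".
- **Secondary (3)** takes the same events one at a time: "Performed separately for each of the four components". The main analysis is "Kaplan-Meier survival estimates; time-to-event regression including fixed effects for minimisation factors and random hospital effect", followed by a bracket, again labelled as a sensitivity analysis, naming "competing risks of non-cardiac death and withdrawal from follow-up".

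The two rows therefore carry the same two-item list. Nothing elsewhere in the article adds cardiac death as a competitor for a component, or says that withdrawals are censored in these analyses. Under Data collection, dates and causes of death come from national electronic records.

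The fatal endpoint is named in two ways. The Abstract, Objectives and Outcome measures speak of cardiovascular death; Table 2 speaks of cardiac death.

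**The concern.** A competing event is one after which the event of interest can no longer happen. Two features of the list do not fit that definition.

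1. **Withdrawal.** A withdrawn patient can still have an infarction, be admitted or die; the trial just does not see it. If withdrawal is coded as competing, the estimate becomes the probability of an event observed before withdrawal, which depends on how many patients withdraw in each arm. The trial is open-label for staff and patients, so unequal withdrawal is possible.
2. **Cardiac death.** Omitting it from the composite's list is correct, because it is part of that endpoint. The list is then carried over to heart failure, non-fatal MI and cardiovascular hospitalisation analysed alone. There cardiac death also ends the possibility of the event. Left off the list, it would be censored while non-cardiac death counts as competing. The resulting incidence refers to a setting in which cardiac deaths do not occur.

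At stake are the absolute risks and subdistribution-hazard estimates from these sensitivity analyses, and the reading of the component results.

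**Working it through.** **The plan's own figure.** The Sample size section states 80% power with 14 clusters of 100 per arm for both co-primaries. With (1.960 + 0.842)² = 7.849:

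- Events: 13% vs 10.4%, y = 100 × 27/12 = 225 person-years per cluster, CV 0.05. Clusters = 1 + 7.849 × [(0.13 + 0.104)/225 + 0.05² × (0.13² + 0.104²)] / 0.026² = 13.88, so 14.
- Therapy uptake: 95% vs 98%, m = 100, CV 0.02. Clusters = 1 + 7.849 × [(0.0475 + 0.0196)/100 + 0.02² × (0.95² + 0.98²)] / 0.03² = 13.35, so 14.

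Both reproduce. This point changes neither; the sample size only supplies the planned "difference in 12 month rates of 13% and 10.4% between standard care and GRACE arms" as a yardstick of 2.6 points.

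**Method for the illustrations.** Constant hazards over one year, withdrawal independent of events. A 12-month risk p corresponds to a hazard −ln(1 − p). With event hazard h and total hazard H (event plus everything coded as competing), cumulative incidence = (h/H) × (1 − exp(−H)). The article gives no withdrawal rate by arm and no cardiac-death rate; those used here are assumptions.

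**A. Withdrawal coded as competing, no true effect.** Risk 13% in both arms, h = −ln(0.87) = 0.1393.

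- Withdrawal 2%: hazard 0.0202, H = 0.1595. Incidence = (0.1393/0.1595) × (1 − 0.87 × 0.98) = 12.87%.
- Withdrawal 8%: hazard 0.0834, H = 0.2226. Incidence = (0.1393/0.2226) × (1 − 0.87 × 0.92) = 12.48%.
- Spurious difference: 0.39 points, and 0.39/2.6 = 15% of the planned difference. With equal withdrawal it is zero. Censoring withdrawals returns 13% in both arms.

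**B. Withdrawal coded as competing, planned effect present.**

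| Withdrawal, control / GRACE | Incidence, control / GRACE | Difference (points) | Ratio |
|---|---|---|---|
| Censored | 13.00% / 10.40% | 2.60 | 0.80 |
| 10% / 10% | 12.35% / 9.88% | 2.47 | 0.80 |
| 10% / 2% | 12.35% / 10.30% | 2.06 | 0.83 |
| 2% / 10% | 12.87% / 9.88% | 2.99 | 0.77 |

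**C. Cardiac death omitted for a non-fatal component.** Non-cardiac death is set to zero, to isolate the one omission.

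| Component risk if cardiac death is censored | Cardiac mortality | Incidence with cardiac death competing | Relative overstatement |
|---|---|---|---|
| 5.00% | 3% | 4.93% | 1.5% |
| 5.00% | 8% | 4.80% | 4.2% |
| 10.00% | 3% | 9.85% | 1.5% |
| 10.00% | 8% | 9.60% | 4.2% |

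For example, 5% and 8%: (0.0513/0.1347) × (1 − 0.95 × 0.92) = 4.80%, and 5.00/4.80 gives 4.2%. If cardiac mortality were 8% in one arm and 4% in the other with the same hazard for the non-fatal event, the proper incidences would be 4.80% and 4.90%; the listed rule would show 5.00% in both.

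**The case against.** **These are sensitivity analyses.** A reader might infer that the clinical co-primary result is itself at risk. The article does not support that: in both rows the competing risks stand inside a bracket labelled as a sensitivity analysis, and the main regression is separate. In secondary (3) the bracket opens in an odd place, but the label and the parallel with the co-primary row make this the natural reading. This stands and limits the weight of the point.

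**No competing-risk model is named.** In a cause-specific hazard model, competing events and withdrawals are all censored, so the hazard ratio is the same whatever the list says. A reader might infer that every treatment-effect estimate is biased; that does not follow. But under that model the step would return the same hazard ratio as a main regression that censors these patients. The step adds something only for cumulative incidence or subdistribution hazards, where both faults apply.

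**The SAP may settle it.** An article may leave competing-risk detail to the SAP. Here, however, Table 2 does not stay silent: it states a list, and the list is wrong.

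**The sizes rest on assumed rates.** This is true. Outcomes come from national records, so an unreturned questionnaire is not loss to follow-up for these events, and the 7% to 10% attrition in the Sample size section is an overall allowance, not a difference between arms. The article gives no ground for expecting a large imbalance.

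**Scope.** Non-cardiac death is the right terminal competitor for the composite and for cardiac death as Table 2 defines them. The omission concerns three of the four components.

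**Conclusion.** The point holds as an error of definition in stated sensitivity analyses. Withdrawal is wrongly classed as a competing risk in both rows, and cardiac death is missing from the list for new-onset heart failure, non-fatal MI and cardiovascular hospitalisation. The main co-primary test and any cause-specific hazard ratio are untouched.

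For cumulative incidence and subdistribution hazards the effect is small to moderate: about 0.4 spurious points in example A, and a planned 2.60-point difference reported as 2.06 to 2.99 points if 10% withdraw in one arm and 2% in the other. With no true effect and equal withdrawal there is no spurious difference. Non-fatal component incidence is overstated only slightly. All of this assumes constant hazards and withdrawal unrelated to events, with rates that the article does not give.

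**What to change.** Amend Table 2, and the SAP to match:

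1. In both rows, remove withdrawal from the competing risks and treat it as censoring. Any check for informative withdrawal should be a separate sensitivity analysis.
2. For the composite and the fatal component, keep as competing all deaths that are not the endpoint death.
3. For new-onset heart failure, non-fatal MI and cardiovascular hospitalisation, name death from any cause as competing, and report cumulative incidence on that basis alongside the planned regression.
4. Use one term for the endpoint death throughout. With cardiovascular death in the text and cardiac death in Table 2, a death that is cardiovascular but not cardiac could be counted either way, or as neither if the terms are mixed. Every death should be either an event or a competing event.

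The cost is a change of wording. No new data are needed, because dates and causes of death are already to be collected, and the sample size does not change.
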